### Recruitment

Consecutive boys or girls with overweight/obesity will be recruited from two public schools if they have received referrals from physician to either a primary- or secondary-care general practitioner in the capital district of Bogotá, Cundinamarca Department, in the Andean region. After completion of the informed consent process, adolescents who are interested in participating will be approached with further information and undergo pre-participation screening to determine contraindications to exercise using a cardiovascular and musculoskeletal checklist (including the patient’s medical history, disease history, and physical fitness). A member of the research team will follow up with a phone call to screen for eligibility and explain the main requirements of the study.

### Blinding and randomization methods

The randomization into the four study arms will be performed by CEMA using a block randomization strategy with a block size of four. Since growing adolescents have an increasing body size and are undergoing developmental changes, a control group is necessary to detect changes due to training. After completing the baseline measurements, eligible participants will be randomly assigned to either the control or exercise training groups. The principal investigator will coordinate the allocation sequence, and randomization will be computer-generated. All participants and study personnel (including investigators, trainers, and statisticians) will be blinded to treatment allocation throughout the trial protocol. Access to the allocation code will be restricted to one study statistician who will not perform the final study analyses. Randomization will be conducted independently using sealed opaque envelopes. These procedures are also detailed in the study operations manual. Moreover, the importance of maintaining the blinding and allocation concealment will be reinforced by regularly scheduled conference calls at the sites and daily meetings with the field investigators (Fig. 1).

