### Blinding and randomization

Each participant will have a 0.25 probability of being assigned to any study group. This assignment will be made through previously constructed balanced blocks. These blocks permit an equi-probabilistic assignment and ensure that each group has the same number of participants. This assignment mechanism will continue until all 100 participants have been assigned to their interventions. The study’s health personnel will act independently of the personnel in the school from where the participants are selected. Therefore, they do not carry out any school activities and their tasks are limited to collecting data for this study. The assignment codes will be maintained in a confidential file in the research center of the coordinating group and will be opened when the study analysis is finished. At the beginning and end of their participation in the study, the primary and secondary outcomes will be determined for each of the patients.

Given that physical exercise is an intervention that cannot be masked from the participants or researchers, professionals who are unaware of each subject’s group assignment will perform the measurement and analysis of the resulting variables. To ensure masking, randomization will be applied through balanced blocks and an alphabetical code will be assigned to each study group. This code will be in the custody of the administrative coordinator of the research group and will not be revealed to the professionals in charge of processing the data until the analysis with coded interventions has terminated.

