### Adherence and compliance

The CEMA research center is responsible for preparing the reports for the safety committee to audit the study’s progress. These reports will include the following information: (a) recruitment and follow-up per person per month and comparison with the pre-established goals, (b) adherence of participants (biochemical markers and data on the degree of compliance and a comparison with the objectives foreseen for the exercise groups, (c) quality control (preferences for certain digits, variability, and values out of range), and (d) intermediate and final, primary, and secondary variables for each group and comparisons among groups with respect to the primary variables and other secondary variables. For the interventions with additional exercise, 75% adherence is expected of the 72 planned sessions, along with at least 70% training compliance.

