### Data quality

To evaluate the veracity of the data from the questionnaires and from the database, an external personnel team assigned to each group will revise the instruments and questionnaires for a random number of participants. The proposal is to review the data from approximately 25% of the participants in each group, and CEMA members will confirm and certify the validity of the data. The CEMA researchers will create a system to access the study data through a private website (http://www.urosario.edu.co/cema/inicio/), from where authorized researchers can download all the forms, databases, and articles published. For security and privacy, a valid ID and password are necessary to access the data and the forms. This web-based system is used to send data to the data manager. As a quality control measure, the principal study data will be reviewed for features such as a preference for certain figures and data variability. All the forms will be entered in duplicate and they will be checked for inconsistencies and missing data. To minimize potential error, a *Manual of Operations* has been drafted. Until the end of the trial, personnel from the groups will have access to all the information from the trial, except for the statisticians and the safety committee.

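### A single block size of four for four arms makes allocations guessable in a trial that cannot be masked, and one sentence claims a blinding that the article elsewhere calls impossible

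*Protocol article*

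**What the plan says.** **Allocation.** The section Blinding and randomization methods says the four arms are filled "using a block randomization strategy with a block size of four". No other size, and no variation of size, is given. The later section Blinding and randomization adds: "Each participant will have a 0.25 probability of being assigned to any study group" and "These blocks permit an equi-probabilistic assignment and ensure that each group has the same number of participants". Recruitment is consecutive at two schools (Recruitment). Assignment follows baseline measurement and uses sealed opaque envelopes. One statistician who does not do the final analysis has access to the allocation code. On the investigator's part the text says: "The principal investigator will coordinate the allocation sequence".

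**Blinding.** The same methods section states: "All participants and study personnel (including investigators, trainers, and statisticians) will be blinded to treatment allocation throughout the trial protocol". The later section begins from the opposite premise: "Given that physical exercise is an intervention that cannot be masked from the participants or researchers". It masks only the professionals who measure and analyse outcomes, using a letter code for each group kept by the administrative coordinator. Study design, setting, and participants calls the trial single-blind, and Data collection and outcome measures has outcomes assessed by blinded personnel.

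**Access.** Data quality says that until the trial ends "personnel from the groups will have access to all the information from the trial, except for the statisticians and the safety committee". Adherence and compliance lists, among the contents of the safety committee's reports, "comparisons among groups with respect to the primary variables and other secondary variables".

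**The concern.** Permuted blocks keep the arms balanced at the price of predictability, and the smaller the block, the higher the price. Four is the smallest block that can hold four equal arms. Here past assignments cannot be hidden: control participants have one ordinary class a week, exercise participants have three extra supervised sessions, and the exercise arms differ in intensity. Staff who follow the sequence can narrow down the next assignment and could steer when a given adolescent is randomized.

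The blinding sentence is a separate error. A reader who takes it at face value would credit the trial with masked participants and trainers, a protection against performance effects that it does not have.

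**Working it through.** **Inputs.** Four arms at probability 0.25 each and balanced blocks (Blinding and randomization); block size 4 (Blinding and randomization methods); 100 participants, 25 per arm (Power calculation and sample size).

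**The plan's own figures.** 100 / 4 = 25 blocks. Each block holds one place per arm, so each arm receives 25 × 1 = 25, and the marginal probability is 1/4. Both figures reproduce.

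**Predictability with a block of four.** Each block is one of 4! = 24 orders. Take an observer who knows the block size and the earlier allocations. At place k, 5 − k arms remain, all equally likely:

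| Place in block | Arms left | Chance of a correct guess |
|---|---|---|
| 1 | 4 | 1/4 |
| 2 | 3 | 1/3 |
| 3 | 2 | 1/2 |
| 4 | 1 | 1 |

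- Average: (1/4 + 1/3 + 1/2 + 1) / 4 = 2.0833 / 4 = 0.521, against 0.25 by chance.
- Certain: one place in four, so 25 of 100. A further 25 (the third places) are down to two arms.
- Control versus any exercise arm: this is known at place k if control has already come up, with probability (k − 1)/4 at places 2 and 3, and always at place 4. (0 + 1/4 + 2/4 + 1) / 4 = 1.75 / 4 = 43.75%.

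**Alternatives.** The first three rows are exact, for an observer who knows the block size. The last is a simulation in which the observer does not know the sizes and guesses the arm used least so far.

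| Scheme | Best guess correct | Certain |
|---|---|---|
| Block of 4 | 52.1% | 25.0% |
| Block of 8 | 47.0% | 14.3% |
| Block of 12 | 44.1% | 10.0% |
| Random mix of 4, 8, 12, undisclosed | about 46% | block ends not known |

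**The blinding statements side by side.**

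| Section | Participants | Investigators and trainers | Outcome assessors |
|---|---|---|---|
| Study design, setting, and participants | single-blind, party not named | not named | not named |
| Blinding and randomization methods | blinded | blinded | blinded |
| Data collection and outcome measures | not stated | not stated | blinded |
| Blinding and randomization | cannot be masked | researchers cannot be masked | unaware of group |

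Only the second row claims masked participants and trainers. The fourth row does not name trainers, but they deliver supervised sessions whose heart-rate target differs by arm, so they cannot be unaware of it.

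**The case against.** **Certainty is conditional.** It needs knowledge of the block size and of all three earlier allocations in the block. The article does not say whether participants start one by one or in batches, nor whether one list serves both schools. If one list does (an assumption), staff who see only one of two equal schools guess right about 29% of the time by picking the least-used arm, or about 34% if they also know the block position; about 3% of allocations are then certain. Envelopes, restricted code access, health staff independent of the schools, and assignment after consent and baseline all narrow the room for selective entry. This stands: 25 of 100 is an upper limit, not a forecast. Envelopes, however, hide only the next card, not what the earlier ones imply.

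**The gain is modest.** Varied blocks lower the average guess only from 52% to about 46%. That is true; the main benefit is that block ends are no longer known.

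**Stronger readings that the text does not support.**
- *Custody of the code is contradictory.* The allocation code held by a statistician and the letter code held by the administrative coordinator may be two different objects. Coordinating the sequence need not mean seeing it. The wording needs reconciling, but no contradiction is proved.
- *The single-blind label is a further conflict.* It agrees with the later blinding section.
- *Trial staff see outcomes by arm.* In the Data quality sentence the group personnel are undefined and the exception can be read in more than one way.
- *Group comparisons for the safety committee are improper.* Such reports are ordinary oversight and may be coded.
- *Randomization should be stratified by school.* Nothing in the article argues for this, and it could make guessing easier for single-school staff: about 45% with stratified 4, 8 and 12 blocks, against about 29% with one shared list of fours.

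**Conclusion.** Two points hold. First, the single block size of four is the most predictable permuted-block choice for four equal arms: the average best guess is 52% against 25% by chance, and up to 25 of 100 allocations are certain. This assumes an observer who knows the block size and has followed the whole sequence; a partial observer does worse. Second, the sentence that blinds participants, investigators and trainers is wrong as written, on the article's own reasoning. This needs no assumption.

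A reader might go on to infer that enrolment was manipulated or that the results are biased. The documents show neither: they show an avoidable opening and a masking claim that the trial cannot meet. The changes should be made, and they are cheap.

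**What to change.** 1. **Block sizes.** For participants not yet randomized, draw a new list with randomly varied block sizes, for example 4, 8 and 12, and do not disclose the sizes. The non-analysing statistician generates and holds it; the investigator, recruiters and assessors have no access. Reword the sentence on the investigator's coordinating role to match. Cost: one new list and a possible imbalance of a few participants per arm. An unfinished last block of 12 can separate two arms by at most 12 / 4 = 3, plus one if the old list is left in mid-block.
2. **Blinding sentence.** In Blinding and randomization methods, replace it with: participants and trainers are not blinded; outcome assessors and the analysing statistician are.
3. **Codes.** State in both blinding sections which code the statistician holds and which the administrative coordinator holds.
4. **Access.** In Data quality, say that personnel who recruit, train or measure do not see outcome data by arm.

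Items 2 to 4 cost only rewording. The safety committee's group comparisons can stay, and no stratification by school is needed for this point. If everyone has already been randomized, item 1 lapses and the report should state the block size used.

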**Fig. 1 Fig1:**
[figure not shown]
CONSORT guidelines flow diagram for enrolment and randomization HEPAFIT Study

### Intervention

Participants will be randomly assigned to the following groups.

#### Standard physical education curriculum

This is the control group (*n* = 25). These subjects will not carry out any intervention different from the physical education class prescribed by the Colombian education legislation (Legislation 115 of 1994, decree 1860 of 1994) [29], which is recognized as fundamental and is consequently obligatory in all educational institutions in the country. This session includes 60 min per week of physical activity at low-to-moderate intensity. However, during this period, education will be offered in lifestyles, hygiene, and diet [30] at no cost to participants. Nutritional counseling will be offered as well.

#### High-intensity physical education class

The high-intensity physical education group (HIPE group, *n* = 25) will follow the standard physical education curriculum plus the Physical Activity Intervention on the Obesity of Schoolchildren (in Spanish, the MOVI-2 program), which is based on a socio-ecological model and targets the school, parents, teachers, and children, focusing on increasing physical activity [31]. MOVI-2 includes basic sports games, traditional games, and other outdoor activities such as running, gymkhanas (which consist of different types of competition with obstacles that make the task difficult), lifting, pushing, wrestling, and hauling (http://www.movidavida.org/), for 60-min sessions three times per week for 6 months with an energy expenditure goal of 300 to 500 kcal/session at 75–85% maximum heart rate (HRmax).

For example, the prescribed energy expenditure during exercise for month 1 is 300 kcal session^− 1^:Conveyors game: Exercise energy expenditure is 9.2 kcal min^− 1^ and exercise duration is 100 kcal per session. Dividing by 9.2 kcal min^− 1^ gives 11 min per session.Four corners game: Exercise energy expenditure is 10.8 kcal min^− 1^ and exercise duration is 100 kcal per session. Dividing by 10.8 kcal min^− 1^ gives 9 min per session^.^Stealing handball game: Exercise energy expenditure is 9.4 kcal min^− 1^ and exercise duration = 100 kcal per session. Dividing by 9.4 kcal min^− 1^ gives 10 min per session.

All playground games will be preceded by a 5-min warm up with endurance or resistance games (i.e., the fastest, the clock, iceman, kangaroo race, etc.). The duration and intensity of all playground games sessions will be verified by a downloadable heart rate (HR) monitor (RS 400; Polar Electro Inc., Woodbury, NY) to achieve the prescribed target HR. All activities will be implemented by monitors with technical qualifications in physical activity and sports, or by sport science graduates, specifically engaged and adequately trained for the program. This protocol is applicable for school-aged boys and girls, independent of the level of skill or their physical aptitude, and is a health-oriented program aimed at balanced physical and psychological development.

The MOVI program uses attractive alternative materials not often used in the subjects’ daily lives or in the standard physical education classes. It is accessible, given that it occurs at the end of the classroom activities in the school’s facilities or nearby. It is free of charge and does not require the provision of any specific equipment. In its first edition, the MOVI program showed a moderate effect on reducing adiposity and improving the lipid profile but did not significantly improve global cardiometabolic risk or lower insulinemia [32]. In the second edition (MOVI-2), the duration and intensity of the sessions were increased and it was shown to enhance the development of muscle strength further. Likewise, analyses showed reduced adiposity in both sexes, and an improvement in the girls’ cardiovascular risk profile (low-density lipoprotein cholesterol or LDL-C and insulin) was observed [33]. The MOVI-2 program sessions that will be used in this work are the following:

Frequency: 3 days per week excluding holidays and vacation periods

Duration: 60 min, structured into 5 min of warm-up, 45 min dedicated to the main training curriculum, and 10 min dedicated to returning to a rest state

Protocol: Each of the sessions will work on activities based on health-related physical fitness (cardiovascular and muscle endurance and flexibility) at an intensity of between 8.0 and 11.7 metabolic equivalents (MET). All the games were performed previously by 32 schoolchildren during sessions of the MOVI-2 program while indirect calorimetry (through a portable gas analyzer), cardiac frequency, and accelerometry were evaluated for each game [34]. In addition, we have previously monitored the implementation of all the games with overweight/obese adolescents from Bogotá (unpublished observations).

#### Low-to-moderate intensity physical education class

The low-to-moderate intensity physical education group (LIPE group, *n* = 25) will follow the standard physical education curriculum. In addition, endurance and resistance games from the MOVI-2 program will be used with a goal to achieve an expenditure of 1500 kcal/week through 60-min sessions, three times per week for 6 months for 300 to 500 kcal energy expenditure per session at 55–75% HRmax:

Frequency: Three times weekly, excluding holidays and vacation periods

Duration: 60 min, structured into 5 min of warm-up, 45 min dedicated to the main training curriculum, and 10 min dedicated to returning to a rest state

Protocol: Each of the sessions will work on activities based on health-related physical fitness (cardiovascular and muscle endurance and flexibility) at an intensity of between 4.0 and 7.0 MET.

#### Plus group

The combined group (*n* = 25) performed the 30-min aerobic training program plus the 30-min resistance training, that involve training program used in both HIPE and LIPE. Each session is developed as described above. Additionally, the standard physical education curriculum was followed. The sum of both interventions should not exceed 1500 kcal/week of energy expenditure. All the study participants in this group will receive a hygiene and dietary management plan that includes educational and nutritional support throughout the study.

After 3 months, the intensity will increase and a different exercise sequence will be used until 6 months of intervention have taken place. The exercise duration will be adjusted to achieve the target average caloric expenditure of 1500 kcal/week. Compliance to the exercise protocol, an essential element of an efficacy study, will be defined as successfully completing >90% of scheduled exercise sessions, maintaining the target exercise HR ± 4 beats min^− 1^ for the prescribed duration of the playground games session. The games proposed for this group are presented in Table 1. It should be noted that diverse variations on the games will be carried out to avoid monotony.

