**Methods/design:**

Altogether, 100 hundred overweight/obese, sedentary adolescents (aged 11–17 years) attending two public schools in Bogotá, Colombia, will be included in a parallel-group randomized controlled trial. Adolescents will be randomly assigned to an intervention group following one of four curricula: (1) the standard physical education curriculum (60 min per week of physical activity, *n* = 25) at low-to-moderate intensity; (2) a high-intensity physical education curriculum (HIPE, *n* = 25), consisting of endurance and resistance games and non-competitive activities, such as running, gymkhanas, lifting, pushing, wrestling, or hauling, for 60-min sessions, three times per week, with an energy expenditure goal of 300 to 500 kcal/session at 75–85% maximum heart rate (HRmax); (3) a low-to-moderate intensity physical education curriculum (LIPE, *n* = 25) consisting of endurance and resistance games and non-competitive activities (e.g., chasing, sprinting, dribbling, or hopping) for 60-min sessions, three times per week with an energy expenditure goal of 300 kcal/session at 55–75% HRmax; and (4) a combined HIPE and LIPE curriculum (*n* = 25). The HIPE, LIPE, and combined interventions were performed in addition to the standard physical education curriculum. The primary outcome for effectiveness is liver fat content, as measured by the controlled attenuation parameter 1 week after the end of the intervention program.

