##### Dietary assessment

To determine the average habitual energy and macronutrient intake, a detailed 24-h diet record will be obtained from each adolescent for one weekday and one weekend day during the 1-week baseline period. Food intake analysis software (FAO/INFOODS, Report of the Technical Workshop on Standards for Food Composition Data Interchange, Rome 2004) and national food composition tables (for specific foods) will be used to analyze the total energy and macronutrient intake of each subject’s 24-h diet. The dietary assessment will be conducted by a registered nutritionist.

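### Dietary support is stated for the control and combined arms only, so four of six pairwise contrasts and the planned interaction mix exercise with diet; the energy goals also contradict each other

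*Protocol article*

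**What the plan says.** **Dietary support.** For control, the section *Standard physical education curriculum* states: "However, during this period, education will be offered in lifestyles, hygiene, and diet". It adds: "Nutritional counseling will be offered as well". For the combined arm, *Plus group* states: "All the study participants in this group will receive a hygiene and dietary management plan that includes educational and nutritional support throughout the study". The HIPE and LIPE sections describe games, frequency, duration and intensity on top of the standard curriculum, and mention no dietary component.

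**Diet measurement.** *Dietary assessment* says that "a detailed 24-h diet record will be obtained from each adolescent for one weekday and one weekend day during the 1-week baseline period". The title of Table 2 covers baseline and post-test, and the table lists both the 24-h record and food frequency questionnaires.

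**Analysis.** *Statistical analysis* plans a test of interaction between HIPE and LIPE on the primary outcome, reported with a 95% confidence interval.

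**Energy.**
- LIPE in the abstract: "with an energy expenditure goal of 300 kcal/session".
- LIPE in its own section: "with a goal to achieve an expenditure of 1500 kcal/week through 60-min sessions, three times per week", with 300 to 500 kcal per session, "at an intensity of between 4.0 and 7.0 MET", in a 45-min main part.
- HIPE: 300 to 500 kcal per session in both places (300 in month 1), at 8.0 to 11.7 MET, with the same 45-min main part.
- *Plus group*: 1500 kcal/week appears first as an amount not to be exceeded and then, in the next paragraph, as the target average.

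**The concern.** A contrast between arms estimates the effect of everything that differs between them. Dietary support can plausibly change liver fat by itself. If control has it and HIPE and LIPE do not, the benefit of those programs over control is understated. If the combined arm has it and the single programs do not, combining looks better than it is. The interaction takes both distortions in the same direction.

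The energy problem is of another kind. The *Background* and *Discussion* present the effect of exercise intensity as an open question, and HIPE versus LIPE is the contrast that bears on it. That contrast can be read as one of intensity only if the reader knows whether the two programs are meant to spend the same energy. The text gives conflicting answers.

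**Working it through.** **1. Support by arm, as written.** Let D = 1 where dietary support is stated: control 1, HIPE 0, LIPE 0, combined 1. Let d be the reduction in liver fat due to support, taken as equal in the two arms that have it.

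| Contrast (reduction in liver fat) | Coefficient of d |
|---|---|
| HIPE − control | 0 − 1 = −1 |
| LIPE − control | 0 − 1 = −1 |
| Combined − HIPE | 1 − 0 = +1 |
| Combined − LIPE | 1 − 0 = +1 |
| HIPE − LIPE | 0 |
| Combined − control | 1 − 1 = 0 |
| Interaction: combined − HIPE − LIPE + control | 1 − 0 − 0 + 1 = +2 |

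Four of six pairwise contrasts are affected. The zero for combined versus control needs the two kinds of support to be equally effective; one is offered and the other is a plan delivered throughout.

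**2. Aliasing.** With H and L as indicators of the HIPE and LIPE components, D = 1 − H − L + 2HL in all four arms. A model with intercept, H, L and HL already uses up the four arm means. Adding D gives five columns of rank 4, so an arm-level adjustment cannot separate support from the interaction.

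**3. Size.** Inputs from *Power calculation and sample size*: difference 5.0, SD 4.1, two-sided alpha 0.025, 25 per arm. The range d = 0.5 to 2 points is an assumption; the documents give no figure.

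- SE of a pairwise contrast = 4.1 × √(2/25) = 1.16
- SE of the interaction = 4.1 × √(4/25) = 1.64
- P(significant) for a contrast with no true exercise effect = Φ(b/SE − z) + Φ(−b/SE − z), where b is the bias. z = 2.241 for alpha 0.025 and 1.960 for a 95% interval.
- Power of HIPE or LIPE versus control = Φ((5.0 − d)/1.16 − 2.241)

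| d | Null combined vs HIPE (or LIPE) significant, nominal 2.5% | Null interaction, 95% interval excludes 0 (bias 2d), nominal 5% | Power, HIPE or LIPE vs control |
|---|---|---|---|
| 0 | 2.5% | 5.0% | 98.1% |
| 0.5 | 3.9% | 9.4% | 94.9% |
| 1 | 8.5% | 23.0% | 88.6% |
| 2 | 30.3% | 68.4% | 63.5% |

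With 10% loss (22.5 per arm, SE 1.73) the interaction column reads 8.9%, 21.2% and 63.8% for d = 0.5, 1 and 2. The 98.1% at d = 0 is what the stated inputs give for one pairwise comparison. The protocol states 80%; that is a separate matter, and nothing here depends on it.

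**4. Energy.** The LIPE weekly goal is reproduced only at the top of its own range: 3 × 500 = 1500 kcal/week, against 3 × 300 = 900 at the bottom and 3 × 300 = 900 from the abstract. HIPE is 900 to 1500 in both places. The abstract therefore puts LIPE at or below HIPE, and the LIPE weekly goal puts it at or above HIPE.

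At an assumed 1 kcal/kg/h per MET, 500 kcal in the 45-min main part at the LIPE maximum of 7.0 MET needs 500/(7.0 × 0.75) = 95 kg. Counting all 60 min at 7.0 MET, warm-up and recovery included, it needs 500/7.0 = 71 kg.

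**The case against.** **The dietary gap is inferred from silence in a condensed article.** HIPE, LIPE and combined all keep the standard curriculum, and the education and counselling are described under that heading. They may therefore be common to all arms. This is a fair reading, and the article does not establish that HIPE and LIPE participants get no support. But the Plus group sentence is expressly about that group. If the control package is common and the plan is an addition, combined still differs from each of the other three arms, and the interaction has bias d instead of 2d (6.1%, 9.4% and 23.0% for d = 0.5, 1 and 2). Only if that sentence merely restates a common package does the problem vanish, and the text does not say so.

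**A reader might infer that no contrast can inform on intensity.** The documents do not support that. HIPE versus LIPE has no stated dietary difference. Exercise versus control was never a contrast of intensity, since weekly volume also differs (60 min against 60 + 180).

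**A reader might infer from the separate MET ranges that HIPE and LIPE cannot spend equal energy.** That assumes equal minutes. The HIPE example derives minutes from energy (11 + 9 + 10 = 30 min for 300 kcal), and *Plus group* adjusts duration to the energy target. At 65 kg, on the same conversion, 300 kcal takes about 35 min at 8.0 MET and 40 min at 7.0 MET; both fit in 45 min. The rise from 300 to 500 kcal may also be a planned progression. The conflict between abstract and body remains, as does the use of one figure as both ceiling and target.

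**A reader might infer that dietary change could not be examined at all.** *Dietary assessment* names only the baseline week, but Table 2 points to post-test as well and lists food frequency questionnaires. The two passages disagree; the measurement is not shown to be absent.

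**The stated aims concern programs.** This is largely true of the aim and the hypothesis, and it makes the fallback below easy to adopt.

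**Conclusion.** The point holds in this form. As written, dietary support differs between arms in a pattern that enters HIPE and LIPE versus control and combined versus HIPE and LIPE, and is inseparable from the planned interaction. HIPE versus LIPE is free of it on the text, and combined versus control is free of it if the two kinds of support are equivalent.

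The size depends on an effect of support that the documents do not give. Over 0.5 to 2 points, false-positive rates are about 4–30% for combined versus HIPE or LIPE (nominal 2.5%) and about 9–68% for the interaction (nominal 5%). Power for HIPE or LIPE versus control falls from 98% to between 95% and 64%. These figures assume the protocol's SD of 4.1, 25 analysed per arm, a normal approximation and equal effect of support in control and combined.

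The energy statements are an internal contradiction, not an established difference between arms. Until they are reconciled, it is unclear whether HIPE versus LIPE compares intensities at equal energy or two whole programs.

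**What to change.** 1. Reconcile the control and Plus group sections with the HIPE and LIPE sections so that lifestyle and dietary support is the same in all four arms. If it is already common, one sentence says so. If it is not, and cannot be made so, do not attribute the four affected contrasts or the interaction to exercise alone.
2. Make *Dietary assessment* agree with the Table 2 title, so that the diet record is also taken at post-test.
3. Reconcile the energy statements in the abstract and in the HIPE, LIPE and Plus group sections with each other and with the stated minutes and MET ranges. No particular goal is endorsed here. State whether HIPE and LIPE are meant to be matched on energy; if they are not, word that conclusion as a comparison of programs, not of intensity.

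The cost is amendment wording, at most the same support for the 2 × 25 = 50 adolescents in HIPE and LIPE, and one repeat diet record that Table 2 already implies. *Trial status* has recruitment running from January to December 2018. For anyone treated before the change, record what support each arm received, because the aliasing cannot be undone at the analysis stage.
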